## Abstract

**Background:**

Mother's physical activity levels are relatively low, while their energy consumption is generally high resulting in 58% of Australian women over the age of 18 years being overweight or obese. This study aims to confirm if a low-cost, accessible playgroup based intervention program can improve the dietary and physical activity behaviours of mothers with young children.

**Methods/Design:**

The current study is a randomized controlled trial lifestyle (nutrition and physical activity) intervention for mothers with children aged between 0 to 5 years attending playgroups in Perth, Western Australia. Nine-hundred participants will be recruited and randomly assigned to the intervention (n = 450) and control (n = 450) groups. The study is based on the Social Cognitive Theory (SCT) and the Transtheoretical Model (TTM), and the Precede-Proceed Framework incorporating goal setting, motivational interviewing, social support and self-efficacy. The six month intervention will include multiple strategies and resources to ensure the engagement and retention of participants. The main strategy is home based and will include a specially designed booklet with dietary and physical activity information, a muscle strength and flexibility exercise chart, a nutrition label reading shopping list and menu planner. The home based strategy will be supported by face-to-face dietary and physical activity workshops in the playgroup setting, posted and emailed bi-monthly newsletters, and monthly Short Message Service (SMS) reminders via mobile phones. Participants in the control group receive no intervention materials. Outcome measures will be assessed using data that will be collected at baseline, six months and 12 months from participants in the control and intervention groups.

**Discussion:**

This trial will add to the evidence base on the recruitment, retention and the impact of community based dietary and physical activity interventions for mothers with young children.

**Trial Registration:**

Australian and New Zealand Clinical Trials Registry ACTRN12609000735257

## Background

Overweight and obesity are important public health concerns. The percentage of Australian women of childbearing age that are overweight or obese has significantly increased over the past decade. In 2007, 44% of Australian women aged between 25 and 34 years were overweight or obese compared to only 26% in 1995 [1].

Childbearing aged women are an important target group for dietary and physical activity interventions as they are at an increased risk of long-term overweight and obesity [2]. Women's increased risk of overweight and obesity after their first and subsequent pregnancies is associated with overweight or obesity prior to pregnancy [3,4], gestational weight gain above the recommended guidelines [5,6], failure to lose gestational weight in an appreciable timeframe or excessive postpartum weight retention [7] and interpregnancy weight gain [8].

Overweight and obese childbearing aged women appear to have a disproportionate risk of maternal, intrapartum, peripartum, neonatal, and postpartum complications [9,10]. If this weight gain continues after childbearing, women will be at increased risk of obesity related chronic conditions such as type II diabetes, high blood pressure, dyslipidaemia, cardiovascular disease and the risk of several major cancers [10]. In addition, maternal obesity may have deleterious effects on the neonate such as macrosomia, increased risk of a range of structural anomalies and of still birth [11].

Research indicates that the mechanisms for interpregnancy and 12 months postpartum weight gain can be due to a range of factors such as lack of nutrition knowledge [12], poor dietary habits and physical inactivity [13,14]. For example, research shows that 96% of females aged 25-34 and 94% of females aged 35-44 consume inadequate fruit or vegetables when compared to the Australian dietary guidelines [1]. Furthermore, despite the known health benefits of physical activity, 30% of women aged between 24 and 34 do not do any exercise, while 44% participate in low intensity activity [1].

The barriers to mothers adopting the recommended physical activity behaviours include lack of social support, lack of time, lack of energy and motivation, procrastination, lack of self-efficacy and childcare and financial constraints [15,16]. The influences on eating habits include convenience, cost, lifestyle preferences, confusion around food messages, nutrition knowledge and environmental factors [17]. Furthermore, common postpartum physical symptoms such as fatigue, headaches, nausea, backache and urinary or bowel problems can inhibit mothers following a healthy diet and physical activity plan [18].

Mothers are an important group within the family unit as they are generally the primary caregiver and help to shape the attitudes and behaviour of their children with respect to food and physical activity. Overweight and obese children are twice as likely to become overweight and obese adults when compared to normal weight children [19]. Mothers can prevent children from becoming overweight and obese as they play a major role in determining the family mealtime environment, and managing the amount and type of food available [20]. Thus, efforts to interrupt this cycle of obesity by targeting interventions at mothers are vital from both a public health perspective. Dietary and physical activity interventions could provide benefits to the mother, her future pregnancies and subsequent generations from becoming overweight and obese [21].

Currently, there are few studies that have reported the effectiveness of behavioural interventions designed to improve physical activity and dietary behaviours [22-26] in mothers with young children. These studies have included small samples and have incorporated limited evaluation measures [23-25], even though the evidence suggests that after childbirth mothers are ready to change behaviours associated with overweight and obesity [27,28].

This paper describes the protocol of a randomized controlled trial to improve the physical activity and nutrition behaviours of mothers with young children (between 0 and 5 years of age) attending playgroups.

## Methods/Design

### Study design

The study is a community based 12 month randomized controlled trial. The study is designed according to the recommendations of the CONSORT statement for randomized trials of nonpharmacologic treatment [29].

The REFRESH study will be conducted over three years (Figure 1). The first year will include formative research, development of the evaluation framework and the intervention. In the second year, participants will be recruited, the intervention will be implemented and data will be collected from participants. The final year will include data collection, data analysis and review of the intervention.

**Figure 1 F1:**
[figure not shown]
**REFRESH Study Design**.

### Study aim

The REFRESH study aims to evaluate the effect of a six month physical activity and nutrition randomized controlled trial for mothers with young children attending playgroups in Perth, Western Australia (WA).

The REFRESH program will focus on behaviour change to meet the Australian physical activity guidelines, by encouraging increased in levels of vigorous, and moderate physical activity, the number of steps taken each day and muscle strength exercises [30,31]. The REFRESH program will also aim to encourage behaviour change to meet the Australian dietary guidelines (improve nutritional intake by increasing fruit, vegetable and fibre intake and decreasing fat and added sugar intake) [32].

### Settings

Playgroups in Australia are informal regular community groups that are set up for babies, toddlers and pre-school children (0 to 5 years). The purpose of a playgroup is to encourage play among children to enhance their social, emotional, physical and intellectual development. Parents and carers also find it a valuable resource as they help establish support networks. Playgroups are run by volunteer parents and carers who get together once a week for a couple of hours. They are held at a variety of venues such as libraries, child and maternal health centres, church halls, kindergartens and schools. Playgroups are supported by National and State organisations [33]. The REFRESH project will be conducted in collaboration with Playgroup WA Inc. [34], as the playgroup will be used as the setting to recruit mothers and implement the project.

### Recruitment and randomisation process

A stratified random sampling procedure will be adopted to recruit participants from 560 playgroups embedded in 106 suburbs (neighbourhoods) within the Perth metropolitan area. Stratification will be conducted by suburb geographical location and Socio-Economic Indexes For Area (SEIFA) scores. SEIFA scores are values derived from income, education level, employment status and skill level [35]. The suburbs will then be randomly assigned to either the intervention group or the control group using a table of random numbers. Control and intervention group suburbs will be arbitrarily matched for low and medium levels of socio-economic status based on the SEIFA scores. The senior Playgroup WA Inc. staff will make phone calls to all registered playgroup leaders, explain the REFRESH project and obtain permission for project staff to contact the playgroup. Project staff will visit the playgroup to further explain the project, obtain consent and allocate participants to the intervention or control group. Intervention group participants will also complete the Physical Activity Readiness Questionnaire [36] and provide a medical certificate if deemed necessary before commencing the program.

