### Sample size determination

In order to detect a 20% difference in physical activity at 80% power and 5% level of significance, sample size of 310 mothers of young children are required at the 6-months post-intervention survey in each of the intervention and control groups. A small effect size (0.2) [37] is assumed for studies on behavioural effects due to the influence of extraneous variables and the subtleties of human performance. Allowing for an attrition rate of 30%, 900 mothers of young children will be recruited into the study. Sample size calculations were determined using Power Analysis and Sample Size software [38].

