### Blinding

It is not possible to blind study project staff to the randomisation process, however, the participants will be blinded as to whether they are in the study or control group. The assessor will be blinded until the comparative data analysis is conducted. Participants will be given codes when recruited and these codes will be used throughout the implementation of the study. The participant codes will be revealed only at the six and 12 month comparative data analysis.

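### The SEIFA matching of suburbs has no stated rule and is not placed before the random draw, so as written it leaves room for discretion once arms are known

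*Protocol article*

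**What the plan says.** All of the allocation text is in the protocol article under *Recruitment and randomisation process*. In the order printed:

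1. The sampling frame. The trial will "recruit participants from 560 playgroups embedded in 106 suburbs (neighbourhoods) within the Perth metropolitan area".
2. Stratification. "Stratification will be conducted by suburb geographical location and Socio-Economic Indexes For Area (SEIFA) scores".
3. The draw. "The suburbs will then be randomly assigned to either the intervention group or the control group using a table of random numbers".
4. Matching. "Control and intervention group suburbs will be arbitrarily matched for low and medium levels of socio-economic status based on the SEIFA scores".
5. The playgroup visit, at which project staff "obtain consent and allocate participants to the intervention or control group".

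Under *Blinding*, the article adds: "It is not possible to blind study project staff to the randomisation process".

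No other section mentions the matching. The article does not say who does it, what makes two suburbs a match, or what becomes of suburbs left without a match or lying outside the low and medium SEIFA bands.

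**The concern.** Randomisation protects the comparison only if the arms analysed are the arms that the random numbers produced. The matching sentence follows the draw, and its subject is suburbs that already carry an arm label. The article's own word for the mechanism is neither random nor rule-based.

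If matching means choosing which labelled suburbs to keep, pair or leave out, someone exercises judgement with the allocation in view. That judgement could respond to anything known about a suburb, such as how convenient it is to reach or how willing its playgroups seem. Features of this kind may be related to the mothers' diet and activity. Balancing or adjusting for SEIFA would not remove selection on them.

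What is at stake is the claim that differences at six and 12 months come from the programme and not from how the suburbs were put together.

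**Working it through.** The plan gives no figure for this step, and its sample size does not depend on it. The check is therefore mainly a reading of the text.

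**Step 1: what the order of the sentences allows.** The draw has a time word (*then*) that places it after stratification. The matching sentence has none. Three readings are open:

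| Reading | Support in the text | Consequence |
|---|---|---|
| Suburbs are paired before the draw | No time word on the matching sentence | Harmless if the pairing follows a rule |
| The sentence restates the stratification | SEIFA is named in both places | Harmless, but the sentence is redundant |
| Suburbs are matched after the draw | The sentence comes after the draw and refers to suburbs by arm | A discretionary step on labelled units |

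Nothing in the article rules out the third reading. Someone following the sentences in sequence would carry it out.

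**Step 2: whether the matching is needed.** SEIFA score and location are already stratification factors. If the draw is made within those strata, SEIFA is balanced by design, up to strata with an odd number of suburbs. Matching afterwards adds nothing. The text does not settle whether the draw is within strata: the section introduces stratification as part of sampling and then moves straight to assignment.

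**Step 3: who could exercise the discretion.** The article does not name who does the matching. The staff it does describe, the project staff, are not blinded to the randomisation. No safeguard against knowledge of the arm is stated for this step.

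**Step 4: how much one suburb weighs.** Inputs: 106 suburbs in the frame (*Recruitment and randomisation process*), 900 mothers (*Sample size determination*) and 450 per arm (*Abstract*). The number of suburbs actually used is not given, so it is varied. Assumption: mothers are spread evenly over suburbs.

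Mothers per suburb = 900 / k; share of one arm = (900 / k) / 450.

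| Suburbs used, k | Mothers per suburb | Share of one arm |
|---|---|---|
| 106 (whole frame) | 8.5 | 1.9% |
| 50 (assumed) | 18 | 4.0% |
| 20 (assumed) | 45 | 10% |

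Each discretionary choice moves a whole group of mothers at once. This is a scale for the exposure and does not estimate bias.

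**The case against.** The strongest reply is that the order is inferred. The matching sentence has no time word, stratify-then-assign is a natural reading of the sentences before it, and the adverb may refer only to where the SEIFA bands were cut. Nowhere does the article say that a suburb is chosen, swapped, dropped or moved once its arm is known. This stands, and it is why the point is conditional.

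It can also be said that a journal article condenses a fuller protocol. That would excuse an omitted detail. Here a procedure is stated, and as stated it permits a non-random step. An analysis plan cannot repair allocation afterwards.

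A reader might infer three stronger things that the document does not support.

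- **That the randomisation has been undone.** The article shows loose wording and a risk, with no evidence of reassignment.
- **That the matching biases the result through socio-economic status.** One could suppose an arm difference of 0.5 SD in socio-economic status and a correlation of 0.2 with the outcome, giving 0.5 × 0.2 = 0.10 SD, half the planned effect ("A small effect size (0.2) [37] is assumed"). Both inputs are invented, and the direction is wrong, because matching on SEIFA tends to make the arms more alike on it. Nor would a few choices produce such a gap if the whole frame were split 53 to 53. The chance SD of the arm difference in mean suburb SEIFA, without stratification, is √(2/53) = 0.19 SD, so 0.5 SD is about 2.6 times that. Swapping two suburbs 2 SD apart shifts the difference by 2 × 2/53 = 0.075 SD, so about seven such swaps in one direction would be needed (0.5 / 0.075 = 6.7).
- **That the analysis wrongly ignores strata or pairs and so has wrong standard errors.** The article's *Statistical analysis* section is one short paragraph, and model terms may properly be left to an analysis plan.

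The instruction that project staff allocate participants at the visit may mean only telling mothers their suburb's arm. It is not relied on here.

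**Conclusion.** The point holds in conditional form. As written, the allocation procedure follows the random assignment of suburbs with a matching step that has no rule and no stated place before the draw. Taken in sequence, it lets suburbs be selected, paired or dropped with the arm known, and so allows selection on features other than SEIFA.

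Its size cannot be stated. It depends on whether the step really follows the draw, how many suburbs are used and how the choices are made, none of which the article gives. If pairing precedes the draw under a rule, or the sentence only restates the stratification, one clarifying sentence disposes of the matter. The change is worth making because the step serves no purpose that stratified assignment does not already serve.

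**What to change.** Replace the assignment sentence and the matching sentence in *Recruitment and randomisation process* with:

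> Within each SEIFA level by location stratum, suburbs will be assigned 1:1 to intervention or control in one step from a pre-generated random list; any pairing is done by a defined rule before the draw, and no suburb is selected, dropped, matched or moved after its arm is known.

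The list should also say how a stratum with an odd number of suburbs is handled.

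If suburbs have already been assigned, report how the matching was done, whether it came before or after the draw, and any departure from the random list.

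The cost is wording and one randomisation list. No further participants or data are needed.

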### Inclusion criteria

Study participants will need to be: (a) women aged 18 or over registered with Playgroup WA Inc.; b) have a child between 0 to 5 years; (c) healthy to the extent that participation in a low-stress physical activity program would not place them at risk; (d) not taken part in any research that involves physical activity or nutrition within the last five years; and (e) not on a special diet.

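### Suburbs are randomised before mothers consent, and no step described keeps the arm concealed until then, so selective recruitment by arm is possible

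*Protocol article*

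**What the plan says.** The section on recruitment and randomisation describes sampling and stratification of suburbs, and then: "The suburbs will then be randomly assigned to either the intervention group or the control group using a table of random numbers". Only after that does it describe telephone calls by senior staff of the playgroup organisation to playgroup leaders, followed by a visit at which project staff explain the study, "obtain consent and allocate participants to the intervention or control group". The next sentence adds a step for one arm: "Intervention group participants will also complete the Physical Activity Readiness Questionnaire [36] and provide a medical certificate if deemed necessary before commencing the program".

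Four other places bear on this:

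- Inclusion criteria, item (c), asks that every participant be "healthy to the extent that participation in a low-stress physical activity program would not place them at risk".
- Data collection gives both arms a self-completed baseline questionnaire and a measuring tape, but a pedometer to the intervention group only.
- Blinding states: "It is not possible to blind study project staff to the randomisation process". The same sentence goes on to say that "the participants will be blinded as to whether they are in the study or control group".
- The abstract (Methods/Design) says: "Nine-hundred participants will be recruited and randomly assigned to the intervention (n = 450) and control (n = 450) groups".

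**The concern.** When clusters are randomised and individuals are recruited afterwards, randomisation protects the comparison of suburbs. It does not protect the comparison of the mothers who enrol, unless enrolment is unaffected by the arm. Here the people who explain the study and take consent can know the arm, and nothing described prevents that knowledge from reaching leaders or mothers. What is on offer differs sharply: six workshops with newsletters, messages and resources in one arm, questionnaires only in the other. Willingness to join could differ with it.

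The wording also leaves the unit and order of allocation unclear. If suburb fixes the arm, staff have no allocation left to make at the visit. The abstract, meanwhile, describes participants who are recruited first and randomised second. A reader cannot tell from the article which procedure will be followed.

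The stake is whether a difference at six or 12 months can be attributed to the programme or partly to who agreed to take part. This has to be settled before recruitment, because later analysis can adjust only for what was measured.

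**Working it through.** **1. Order and unit of allocation**

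| Step | Recruitment and randomisation section | Abstract |
|---|---|---|
| Unit randomised | Suburb | Participant, on a plain reading |
| When | Before leaders are called and mothers consent | After recruitment |
| Role of visiting staff | Explain, consent, allocate | Not stated |

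The two accounts differ in both unit and order. The arm-specific baseline packs support the first account, since the arm must be known when the pack is handed over. The order is read from the sequence of the text and from those packs. Figure 1, which might show a timeline, is not available.

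**2. Concealment up to consent**

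- Recruiting staff: stated not to be blinded to the randomisation process.
- Leaders: the text does not say whether the call discloses the arm.
- Mothers: stated to be blinded, but no mechanism is given.
- Eligibility: item (c) covers everyone, while the readiness questionnaire and possible certificate apply to one arm. The two passages need to be reconciled.
- Stratification and matching on the socio-economic index balance suburbs, not which mothers consent.

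**3. The plan's benchmark**

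For a standardised effect d = 0.2 and 80% power, n per arm = 2(z_alpha + z_beta)² / d².

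- One-sided 5%: 2(1.645 + 0.842)² / 0.04 ≈ 309.1, rounded up to 310. This matches the plan.
- Two-sided 5%: 2(1.960 + 0.842)² / 0.04 ≈ 392.4, rounded up to 393. This does not match.
- Attrition of 30%: 310 / 0.70 = 442.9, so 443 per arm or 886 in total, consistent with 900.

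The sidedness is a separate matter. Only the 0.2 and the 310 per arm are used below.

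**4. How large selective recruitment could be (illustration)**

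Assumptions, none from the documents: motivation is normally distributed; the least motivated fraction refuses in one arm and there is no such refusal in the other; motivation correlates 0.3 with the outcome; there is no baseline adjustment.

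If a fraction k stays, mean motivation in that arm rises by φ(z)/k SD, where z is the cut-off. Multiplying by 0.3 gives the shift in the outcome.

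| Refuse | k | Motivation shift (SD) | Outcome shift (SD) |
|---|---|---|---|
| 10% | 0.9 | 0.195 | 0.06 |
| 20% | 0.8 | 0.350 | 0.10 |
| 30% | 0.7 | 0.497 | 0.15 |

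The middle row is half the design effect size (0.10 / 0.2).

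**5. Effect on the false-positive rate**

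Take 310 per arm, SD 1, no true effect, no clustering and a two-sided 5% test. The standard error is √(2/310) = 0.0803. A shift b gives a rejection rate of P(Z > 1.96 − b/0.0803) + P(Z < −1.96 − b/0.0803):

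- b = 0.05: 9.5%
- b = 0.10: 24%
- b = 0.15: 46%

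**The case against.** The strongest reply has five parts.

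- **Knowledge of arm.** A reader might infer that leaders and mothers decide to join knowing their arm. No passage says so. The Blinding section says the opposite of participants, and the visit sentence puts consent before allocation. This stands against the inference. It does not close the gap, because no means of keeping the arm concealed is described, and arm-specific screening, pedometers and workshops make participant blinding hard to sustain.
- **Overridden randomisation.** A reader might infer that staff reassign mothers regardless of suburb. The wording may mean only that staff tell mothers their suburb's arm. That reading is plausible and removes the conflict within the section, but the conflict with the abstract remains.
- **Screening out.** A reader might infer that less fit mothers are removed from the intervention arm. The article places the readiness step before the programme starts and does not say that a mother without a certificate leaves the trial or its analysis. The asymmetry is real; exclusion is not shown.
- **Biased baseline measurement.** A reader might infer that unblinded staff assess baseline. It is self-completed, and the article does not say who judges the readiness form. The point about staff knowledge is confined to consent and allocation.
- **Inevitable inflation.** Outcomes are measured at baseline in both arms and repeated-measures models are planned, so some imbalance can be seen and adjusted for. Fitter or keener recruits might also have less room to improve, so the direction is not established. What stands of the concern is that adjustment may not reach unmeasured differences such as motivation.

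The Discussion also expects playgroup recruitment to encourage all members to register. If that happened equally in both arms, selection within playgroups would be small. It is an expectation, not a safeguard.

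**Conclusion.** The point holds as a risk that the described procedure leaves open, not as demonstrated bias. Suburb randomisation before consent, unblinded recruiting staff, arm-specific baseline packs and a one-arm readiness check are all in the text, as is the conflict with the abstract. Concealment of the arm until consent is not described, and participant blinding is asserted without a mechanism.

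Size and direction are unknown. The range of about 0.06 to 0.15 SD rests wholly on assumed one-arm refusal of 10% to 30%, sharp truncation and a correlation of 0.3, before baseline adjustment. It shows only that plausible selection need not be negligible beside an effect size of 0.2. The false-positive rates additionally ignore clustering.

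**What to change.** 1. Reconcile the abstract with the recruitment section so that both say suburb alone determines arm. Replace the wording about staff allocating participants with wording that staff inform them of their suburb's arm.
2. Use one neutral script for leaders and mothers in both arms. Complete playgroup permission, consent and the same check of criterion (c) in both arms before the arm is disclosed. The content of that check stays with the investigators.
3. Have the baseline questionnaire completed before disclosure, ideally at the visit. Take the pedometer out of the intervention baseline pack and hand it over only after disclosure.
4. Analyse all consented mothers in the arm of their suburb, whatever the outcome of the certificate step.
5. Report consent rates by arm, so that readers can judge whether recruitment differed.

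The cost is one extra short form for control mothers and a short delay before disclosure. Because questionnaires are now returned in a self-addressed envelope, waiting for them could mean a further contact with each playgroup; completion at the visit would avoid most of this.
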